Integration of mental health care into primary care is most likely to work well using existing systems of management and supervision as a starting point. Partners In Health (PIH), a non-profit organization working in twelve countries, has been supporting the public health delivery system in three rural districts of Rwanda since 2005. In collaboration with the MOH, PIH/IMB (Inshuti Mu Buzima) has implemented the MESH program (Mentoring and Enhanced Supervision at Health Centers) to improve the quality of care provided by nurses at first level health facilities in IMB supported districts of Rwanda. MESH supports health center nurse implementation of key child and adult clinical protocols by incorporating decentralized didactic training with ongoing clinical mentorship and quality improvement activities at health centers. The model follows closely with World Health Organization (WHO) clinical mentoring guidelines developed for effective task shifting of HIV care. Initial results from the MESH program demonstrate significant improvement in a number of quality-of-care indicators after mentoring. The MESH program is currently being brought to scale nationally for HIV care in all forty one districts in Rwanda, with preliminary plans in place for further future scale up in other clinical domains.

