### **Methodology**

#### ***Process Evaluation: routine quantitative program data***

Routine program monitoring data will be collected for three months prior to and six months following the implementation of the MESH program, to assess whether increases in mental health diagnoses occur in relation to implementation of MESH. An increase in the number of visits following MESH implementation will be interpreted as an increase in uptake of mental health services.

All health centers participating in the MESH program in Burera district will be surveyed. At each health center, the total number of patients with a mental disorder seen at each health center per month, the number of new patients diagnosed with a mental disorder each month, and the number of patients who receive any follow-up over the course of six months will be recorded. In addition, demographics (including age, gender and village), and the diagnosis and treatment as

recorded in the health center register, will be documented for each patient. These routine data will also be collected from the Butaro district hospital outpatient mental health clinic to assess district wide service use.

Patient diagnoses and visit data are currently routinely recorded in the daily register by clinicians at all health facilities in the district. Each month, a research data officer will travel to participating health facilities and record these process indicators. The data will be entered into an electronic patient database currently in use by the IMB MH team for tracking routine process indicators. A subset of these data will be routinely reviewed for accuracy and completeness by the PI by comparing them with the paper registers at the participating facilities. The database is held on a team computer which is password protected and kept by the IMB MH team at Butaro hospital.

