*Data analysis:* We will compare the number of new patients diagnosed with a mental disorder, the number of new mental health diagnoses, the number of mental health follow-up visits, and % of patients with specific diagnoses pre- and post- MESH MH program implementation. We will also compare new and follow up data from health centers with routine data from the district mental health clinic. We hypothesize that we will observe an increase in the number of mental health diagnoses and follow-up visits at health centers post-MESH implementation, representing an increase in uptake of mental health services and recognition of mental health morbidity among providers. We further hypothesize that MESH training will lead to improvements in the number of individuals with specific mental health diagnoses post-MESH.

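### A rise in raw counts of mental health diagnoses and follow-up visits is read as better provider recognition, but without all-cause attendance the counts support a reading of uptake only

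*Protocol*

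**What the plan says.** Under *Process Evaluation: routine quantitative program data*, the protocol lists what the data officer takes from each health center: "the total number of patients with a mental disorder seen at each health center per month", then "the number of new patients diagnosed with a mental disorder each month, and the number of patients who receive any follow-up" over six months, with demographics, diagnosis and treatment for each such patient. The period is three months before and six months after implementation. The source is the register: "Patient diagnoses and visit data are currently routinely recorded in the daily register by clinicians at all health facilities in the district".

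The data analysis paragraph of that section sets out the comparison: "We will compare the number of new patients diagnosed with a mental disorder, the number of new mental health diagnoses", follow-up visits, and the percentage "of patients with specific diagnoses pre- and post- MESH MH program implementation". The hypothesis is that "we will observe an increase in the number of mental health diagnoses and follow-up visits at health centers post-MESH implementation", and the meaning of that rise is fixed in the same sentence: "representing an increase in uptake of mental health services and recognition of mental health morbidity among providers".

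Earlier in the section, a rise in visits is to be interpreted as uptake alone. Aim 1, under *Study goals and objectives*, is also framed as change in uptake.

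**The concern.** Recognition by providers is a statement about a share: of the people a nurse sees, in how many is a mental disorder identified? The plan records how many were identified but not how many were seen. A count can rise because nurses recognise more, because more people attend, or because more people with a known or suspected disorder come for care. The stated reading credits any rise to recognition as well as to uptake. A fall in attendance could equally hide a real gain.

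The consequence lies in what may be concluded. *Limitations* relies on the process evaluation to make attribution to the program more plausible in a study without a control group, and *Dissemination of Results and Publication Policy* links positive results to recommendations for scale-up. A recognition claim that the data cannot carry would enter that argument.

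This cannot be left to a statistical analysis plan, because the protocol fixes both the extraction list and the interpretation, and no later analysis can use a variable that was not collected.

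**Working it through.** The protocol gives no attendance figure, baseline count or power calculation for this evaluation, so there is no figure of its own to reproduce. The check has two parts.

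**1. Does any planned item supply the missing denominator?**

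- Patients with a mental disorder seen per month: no. This is itself a product of recognition.
- New patients diagnosed, and patients with follow-up: no. Both are numerators.
- The percentage with specific diagnoses: its denominator is not stated. On the recorded data it can only be case mix among mental health patients.
- The Butaro outpatient mental health clinic series: the same kind of mental health data, with no general attendance.
- The supervision checklists (*Process Evaluation: routine quantitative quality of care data*): these record whether the nurse made a diagnosis and whether the mentor agreed, but only in directly observed cases. No pre-implementation comparison is stated.

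**2. What can the count distinguish?**

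Let *a*, *r* and *c* be the post/pre ratios of monthly attendance, of the share recognised among general attendees, and of direct care-seeking for mental disorders. Let *s* be the baseline share of diagnoses that arise among general attendees, the rest coming from people who present because of their disorder. Taking direct care-seekers as a small part of all consultations and diagnosed at an unchanged share:

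- count ratio = *s* × *a* × *r* + (1 − *s*) × *c*
- ratio of diagnoses per consultation = count ratio / *a*

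All values below are assumptions. Rows with *s* = 1 are the case of full proportionality to attendance.

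| *s* | *a* | *r* | *c* | Count ratio | Rate ratio |
|---|---|---|---|---|---|
| 1 | 1.1 / 1.2 / 1.3 | 1 | – | 1.10 / 1.20 / 1.30 | 1.00 |
| 1 | 1 | 1.2 | – | 1.20 | 1.20 |
| 1 | 0.8 | 1.25 | – | 0.8 × 1.25 = 1.00 | 1.25 |
| 0.5 | 1.2 | 1 | 1 | 0.6 + 0.5 = 1.10 | 1.10 / 1.2 = 0.92 |
| 0 | 1.2 | – | 1 | 1.00 | 1 / 1.2 = 0.83 |
| 0.5 | 1 | 1 | 1.4 | 0.5 + 0.7 = 1.20 | 1.20 |

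A count ratio of 1.20 arises from attendance alone, from recognition alone or from care-seeking alone, so the count cannot tell them apart. With 20% more attendance and unchanged recognition, the spurious rise runs from 0% (*s* = 0) to 20% (*s* = 1). The rate removes the attendance effect when *s* = 1. It still rises with care-seeking (last row), and it falls without any loss of recognition when unrelated attendance grows (*s* = 0 and 0.5).

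**The case against.** The strongest objections are these.

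- **Recognition is a side remark.** Aim 1 and the rule for reading visits speak of uptake. Recognition appears in one clause of a hypothesis, without its own endpoint or test, inside an evaluation described as an adjunct. This stands and limits the weight of the point. It does not remove it, because the clause says what a positive result will be taken to mean.
- **Diagnoses need not follow attendance.** *Quantitative outcomes evaluation* describes a weekly mental health clinic day, and the target disorders include schizophrenia and epilepsy. Many patients may come because of their illness. This stands: a reader might infer that counts move one-for-one with attendance, but that is an assumption the documents do not establish. Direct care-seeking is, however, a second reason why a rise need not mean recognition.
- **The program need not change attendance.** A reader might infer from *Background and Rationale*, where "MESH supports health center nurse implementation of key child and adult clinical protocols", that other MESH services shift general attendance. That section reports quality-of-care gains and says nothing about attendance, and no section says other MESH services start or change at the pre/post boundary. The inference is unsupported and is not relied on here.
- **A rate is no measure of recognition either.** This stands. Diagnoses per consultation also move with care-seeking, with transfer of patients from the district clinic and with seasonal illness.
- **The checklists bear on diagnosis.** They do, and they do not depend on attendance. They cover observed cases only, so they complement the counts but do not repair the reading placed on them.

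**Conclusion.** The point holds in a limited form. The raw counts are a reasonable measure of uptake. They do not identify recognition by providers, because patients seen for any reason are not recorded and nothing else in the plan fills that gap. This conclusion rests on the extraction list and the stated interpretation alone, and needs no numerical assumption.

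The size of any error is unknown. The illustration (0% to 20% spurious rise for 20% more attendance; a 25% gain hidden by a 20% fall under full proportionality) rests on assumed attendance changes and an assumed share of diagnoses that scale with attendance.

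Three stronger readings should be avoided. It is not true that no patient volume is recorded: patients with a mental disorder seen each month are. Aim 1 as an assessment of uptake is not undermined. The primary outcomes, mental health status and daily functioning, are unaffected.

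**What to change.** 1. In the data analysis paragraph of *Process Evaluation: routine quantitative program data*, limit the reading of a rise in raw counts to uptake and delete the clause on recognition among providers. This costs nothing, needs no data and resolves the defect by itself.
2. Where the daily register yields it, have the data officer also record total adult consultations per center per month for the same nine months (three before, six after). Report new mental health diagnoses per 1,000 consultations beside the counts, labelled as an attendance-adjusted supporting measure and not as proof of recognition. State that it also moves with direct care-seeking, transfer from the district clinic and seasonal illness.

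The second step costs one more figure per center per month and one more analysis line. The protocol says that the register holds diagnoses and visit data but does not confirm that all-cause totals can be taken from it, so this should be checked first. If they cannot, the first step is sufficient.

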***Process Evaluation: routine quantitative quality of care data***

Specific indicators of quality have been developed to track each nurse's provision of mental health care at health centers as an integral routine part of the MESH program. These quality of care indicators will be routinely collected over one year using the MESH supervision checklist, completed by mentors. Each month, all MESH mentor observation checklists are collected from the MESH nurse mentor and entered into a database. The quantitative process indicators for purposes of this evaluation will include a subset of routinely collected indicators and will include: the number of MESH checklists completed each week (indicating the number of directly observed cases), as well as the results from six dichotomous and two summed data points from each supervision checklist:

For new patients:

- 1) Did the nurse make a diagnosis?
- 2) Did the mentor agree with the diagnosis?
- 3) Safety questions
- 4) Summary score of treatment planning- non medication
- 5) Summary score of treatment planning- medication management
- 6) Did the nurse make a follow-up appointment?

*Data analysis:* For each nurse mentee from each health center, we will calculate the change in checklist score each month relative to baseline and test whether the mean change is different than zero. We hypothesize that within person change will increase with time since MESH implementation. For binary variables, we will examine whether proportions increase with time since MESH enrollment. We will adjust for correlation resulting from repeated measures from the same individuals.

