### *MESH Mental Health Program*

MESH provided a robust platform through which to translate the national policy of decentralized mental health care into action and create a scalable model for primary care mental health services in rural Rwanda. In August 2012, IMB partnered with the MOH in Burera district, northern Rwanda, to integrate mental health care into health center primary care services using the MESH platform. Burera district is served by Butaro hospital, a 150-bed public hospital with approximately thirty five general nurses, thirteen full time general practitioners, four psychiatric nurses and one psychologist. The hospital is the primary referral center for seventeen health centers, and serves an overall population of approximately 340,000 people.

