### ***Qualitative outcomes evaluation***

*Study Population/Recruitment:* A subset of patients recruited for the quantitative program evaluation will be purposively selected for the qualitative program evaluation. Approximately 40-50 “information rich” (e.g. willing and able to speak freely about their experiences) participants will be chosen by the clinician researcher or recommended by the health center nurse or the MESH mentor. The interviews will occur between October 2014 and July 2015. Selected

patients and their accompanying family member will be invited to participate in the semi-structured interview by the clinician researcher at the second or third follow up for the quantitative evaluation.

*Nurses:* All health center nurses (approximately eight nurses) participating in the MESH MH program at the four selected health centers will be invited to participate in the qualitative program evaluation by the trained clinician researcher or the PI. The nurses will be invited sequentially to participate during the nine month period (October 2014 to May 2015) following the initiation of the MESH MH program.

*Data Collection and Measurement:* Demographic data of participants will be obtained. Semi-structured interviews will be conducted by the mental health clinician researcher who will be trained and supervised by the PIs. The interviews will be conducted in Kinyarwanda and audiotaped, and the interviewer will take notes for context and non-verbal communication. The interview guide will be developed through an emergent design including insights gained from the investigator's experience working as a psychiatrist in Burera district for two years, as well as insights from other mental health workers in Rwanda and the literature on primary care integration models for mental health.

The semi-structured interviews will include sections to discuss access to and uptake of care, quality of care and outcomes for patients of the MESH MH program, as well as the health center nurse as an agent of delivery and overall experiences of the MESH mentorship model of care, including perceived needs for improvement. Interview guides will be tailored to the nurses, users and families, probing for experiences and opinions in each section. Interviews will be translated into English and transcribed for analysis.

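### The test named for the summed checklist scores has no time term, so it cannot show the growth over time that the protocol hypothesizes

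*Protocol*

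**What the plan says.** The data analysis paragraph of the Protocol section 'Process Evaluation: routine quantitative quality of care data' has four parts.

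- **Test for scores:** for each nurse mentee, "we will calculate the change in checklist score each month relative to baseline and test whether the mean change is different than zero".
- **Hypothesis for scores:** "We hypothesize that within person change will increase with time since MESH implementation".
- **Binary items:** "For binary variables, we will examine whether proportions increase with time since MESH enrollment".
- **Correlation:** "We will adjust for correlation resulting from repeated measures from the same individuals".

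On data collection, the section says: "These quality of care indicators will be routinely collected over one year using the MESH supervision checklist, completed by mentors". Two of the data points taken from each checklist are summed scores (non-medication and medication treatment planning), and the test applies to these. The protocol gives no nurse number, standard deviation, expected trajectory or power for this analysis.

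**The concern.** The hypothesis concerns a trend: change from baseline should become larger as mentoring continues. The null hypothesis of the named test is that mean change equals zero, which says nothing about how change develops over the year. Scores that step up once and stay flat, or jump and then slip back, violate that null just as a steady climb does. Adjusting for repeated measures corrects the standard error but leaves the tested hypothesis as it was.

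The study has no control group, and the Limitations section relies on the process evaluation to make it more plausible that clinical change is due to MESH. Growth under continued mentoring would support that more specifically than a single shift after baseline. A significant mean change could be reported as confirming growth that was never tested.

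**Working it through.** **No figure to reproduce.** The protocol states no sample size or power for this analysis, so the check compares what each test responds to.

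**Inputs**
- Duration: one year (from the section), taken as month 0 plus months 1 to 12.
- Nurses: the number in the checklist analysis is not stated. The qualitative section gives "All health center nurses (approximately eight nurses) participating in the MESH MH program at the four selected health centers", so 8 is used. The upper range is 34, from 17 centers ("The hospital is the primary referral center for seventeen health centers") times 2 nurses each (8/4).
- Assumed: residual SD σ = 1, one score per nurse-month, independent residuals, two-sided 5%. The between-nurse SD of the 12-month gain, τ, is 0 unless stated.

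**Formulas.** Each test is a one-sample t-test on one summary per nurse. Its noncentrality is δ = (true mean of the summary) × √(n / variance), and power comes from the noncentral t distribution with n − 1 degrees of freedom.
- Average change over months 1 to 12: variance = 1 + 1/12 + (6.5τ/12)².
- Slope over months 1 to 12: variance = 1/143 + (τ/12)², where 143 is the sum of squared deviations of the months.
- Slope over months 0 to 12: the same with 182 in place of 143.

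**One-off step of 1 SD, then flat (n = 8)**
- Mean change: δ = 1 × √(8/1.0833) = 2.72, rejects 65%.
- Slope, months 1 to 12: δ = 0, rejects 5%.
- Slope, months 0 to 12: true slope 6/182 = 0.033, δ = 0.033 × √(8 × 182) = 1.26, rejects 19%. With 34 nurses this becomes 71%.

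**Jump of 1.5 SD, then a fall of 1/12 SD per month (score 1.5 − m/12 at month m)**
- Average change = 1.5 − 6.5/12 = 0.958, δ = 0.958 × 2.72 = 2.60. Mean change rejects 61%, although change is shrinking throughout.

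**Steady rise of 1 SD over 12 months**
- Mean change: average 6.5/12 = 0.542, δ = 0.542 × 2.72 = 1.47, power 25%.
- Slope, months 1 to 12: δ = (1/12) × √(8 × 143) = 2.82, power 68%.
- Slope, months 0 to 12: δ = (1/12) × √(8 × 182) = 3.18, power 78%.
- With τ = 0.5: mean change 24%; slope over months 1 to 12, 58%.
- With τ = 1: 20% and 41%.

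**Rise to 1 SD by month 3, then a plateau**
- Average change = (1/3 + 2/3 + 10)/12 = 0.917, δ = 2.49, power 57%.
- Slope over months 1 to 12, 19%; over months 0 to 12, 49%.

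| Trajectory (n = 8, τ = 0) | Mean change | Slope, months 1–12 | Slope, months 0–12 |
|---|---|---|---|
| 1 SD step, then flat | 65% | 5% | 19% |
| Steady 1 SD rise | 25% | 68% | 78% |
| Plateau from month 3 | 57% | 19% | 49% |

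The test is two-directional, so a steady 1 SD decline is also rejected 25% of the time.

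**More nurses.** With 16 nurses, mean change rejects the step 95% of the time, and power for the steady rise is 50% against 96% for the slope over months 1 to 12. With 34 nurses the corresponding figures are 100%, 84% and about 100%. A larger sample makes the mean-change test more likely to reject on a pure step; it does not turn it into a test of growth.

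**The case against.** **Mean change is relevant.** If change grows upward from baseline, its mean is above zero, so the test checks a consequence of the hypothesis. Aim 2 asks whether nurses deliver basic quality care and mentions no trend, so a sustained jump is real improvement under that aim. This stands. A reader might infer that the test has no bearing on the hypothesis, but that goes too far: it addresses improvement and cannot establish growth.

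**Power.** A reader might infer that the named test is generally weak. The documents do not support that. They state no trajectory, and intensive training comes before supervision, so an early gain followed by a plateau is plausible. In that case mean change has the most power of the three tests.

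**Multiplicity.** The sentence could be read as a separate test each month. In simulation, at least one of 12 such tests then rejects in about 34% of runs when nothing changes. But the sentence speaks of a single mean change, and the adjustment for repeated measures points to a joint analysis. The figure is not part of this point.

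**A slope is not automatically better.** A slope that includes baseline also reacts to a pure step (19% with 8 nurses, 71% with 34). This stands, and it determines the form of the fix.

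**Left to the analysis plan.** Model form and time coding usually are. Here, though, the protocol names a test, and that test does not match the hypothesis in the next sentence.

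**Conclusion.** The mismatch holds on the wording alone and needs no assumed number: the hypothesis is about growth with time, and the test named for the scores contains no time. The binary items in the same paragraph do get a trend.

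The size of the consequence rests on the assumed nurse number, SDs, one score per nurse-month and trajectory. Since completed checklists are counted weekly, a month may hold several, which would make the baseline less noisy than assumed. With 8 nurses and τ = 0, the named test rejects about 65% of the time after a step with no later growth, and has about 25% power for a steady rise, against 68% for a post-baseline slope.

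No claim is made about power in general. The patient outcomes are primary, the process evaluation is an adjunct, and the Limitations section already restrains causal claims. The point should be corrected but is modest in weight.

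**What to change.** For each of the two summed scores, fit one repeated-measures linear mixed model to all monthly scores including baseline. Use a post-baseline step and months since MESH implementation as fixed effects, nurse-level random effects, and a small-sample correction. Name the time slope as the single test of the growth hypothesis and report its 95% CI. The step term must be in the model from the start, because otherwise a one-off shift feeds into the slope. With it included, the slope rests on months 1 to 12, so the relevant power under a steady rise is about 68% rather than 78%.

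Keep mean change from baseline with its CI as the estimate of overall improvement for Aim 2, and show month-by-month changes descriptively, without tests.

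The cost is a rewritten paragraph and a standard model on data already being collected. The drawback is that the model assumes a roughly linear post-baseline trend and has low power for growth if gains come early and level off (19% in the plateau example).

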## **Executive Summary**

*Background:* A comprehensive evaluation of the IMB Mental Health program's innovative model of integrated mental health care at health centers (MESH MH) is needed to provide feedback for ongoing implementation and growth of the program. Evidence of increased uptake and acceptable quality of care by health center nurses, as well as improved patient clinical outcomes, must be documented before scale up of the MESH MH program to a national level could be considered.

*Objectives/Methods:* A mixed-methods outcomes evaluation with a pre- and post-test design will be performed at four purposively selected health facilities participating in the MESH MH program. Qualitative and quantitative outcome evaluations will be conducted to determine whether patients who receive mental health care at supported health centers (HCs) experience clinical and functional improvement and to explore the perspectives and experiences of health workers and patients who receive care through this program. As an adjunct to these evaluations, a process evaluation will be conducted using service utilization data to assess changes in uptake of mental health services at participating health facilities within the district, and use MESH supervision checklists to determine whether participating HC nurses adequately provide basic quality mental health care.

*Population:* Routine program monitoring data will be collected from the registries for all patients attending mental health services at district health centers and outpatient mental health clinic. All adults arriving for a mental health visit at selected health centers who are diagnosed with a neuropsychiatric disorder will be asked to participate in the quantitative portion of the evaluation. Patients who need to be transferred to the district hospital for an acute medical or psychiatric emergency and patients with a primary alcohol or substance use disorder will be excluded from the evaluation. Approximately eight nurses and fifty "information rich" patient and family participants will be selected purposively for the qualitative evaluation.

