Three health centers in Burera district were initially chosen to pilot the MESH mental health (MESH MH) program. Four major neuropsychiatric disorders were chosen for clinical focus based on needs perceived by district mental health staff and health center directors, informal observation of diagnoses as listed in health center registers, and evidence of disease burden and treatment effectiveness as defined by the World Health Organization (WHO): schizophrenia, bipolar disorder, major depressive disorder, and epilepsy. After an intensive, forty-hour training designed to teach primary care nurses how to identify and manage these four disorders, a program of regular supervision by a trained Rwandan mental health nurse was initiated. Health center supervisory visits included clinical observation, individual case review, documentation review, and brief didactic sessions. A mental health supervision checklist was adapted from other MESH areas of clinical focus, to assist with clinical mentoring and to ensure standardization of activities across clinical domains. The mentor nurse used the case observation checklist to ensure that health center nurses were performing key elements of basic psychiatric evaluations, accurately diagnosing patients and offering appropriate treatment and support based on diagnosis. The successful completion of checklist items during mental health clinical evaluations was used to define basic quality of care provided by health center nurses. During each supervision session, the nurse-mentor also discussed systems based performance issues and “quality gaps” with the health center director and the health center nurses, and formulated specific plans to improve patient care, referral pathways, coordination between services, and other systems level issues.

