### **Study goals and objectives**

Aim 1: Assess changes in uptake of mental health care by assessing the quantity and quality of mental health diagnoses at Burera district health centers in relation to the implementation of the MESH MH program.

Aim 2: Assess whether participating non-specialist health center nurses offer basic quality mental health care as specified in MESH MH program objectives.

Aim 3: Assess whether patients who receive mental health care at select health centers experience clinical and functional improvement, including economic status

Aim 4: Explore the perspectives and experiences of health center nurses, families and patients who receive care at select health centers where the MESH MH program has been implemented

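### Aim 2 asks whether nurses' care reaches a basic standard, but the planned checklist analysis tests only change over time and so cannot answer it

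*Protocol*

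**What the plan says.** **The question.** The protocol's Study goals and objectives section states Aim 2 as: "Assess whether participating non-specialist health center nurses offer basic quality mental health care as specified in MESH MH program objectives". The Executive Summary gives the checklists the same job, to "use MESH supervision checklists to determine whether participating HC nurses adequately provide basic quality mental health care". It also names what must be documented before national scale-up is considered, including "Evidence of increased uptake and acceptable quality of care by health center nurses". The Program Research Evaluation section repeats that condition.

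**The definition.** The MESH Mental Health Program section, describing the pilot, says: "The successful completion of checklist items during mental health clinical evaluations was used to define basic quality of care provided by health center nurses". It gives no cut-off or required share of items.

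**The analysis.** The section on routine quality of care data collects six binary and two summed data points per checklist over one year. For each nurse, "we will calculate the change in checklist score each month relative to baseline and test whether the mean change is different than zero". The hypothesis follows: "We hypothesize that within person change will increase with time since MESH implementation". For the rest: "For binary variables, we will examine whether proportions increase with time since MESH enrollment". The section adds that correlation between repeated measures on the same person will be adjusted for.

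**The concern.** The aim, the Executive Summary and the scale-up condition all ask whether care is good enough. The analysis asks whether it is getting better. These are different quantities, and the second does not determine the first. A group of nurses can improve clearly and still omit most of what the checklist requires. Another group can complete nearly all of it from the start and show no change.

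At stake is the quality part of the case for scale-up. If the evaluation reports only what this section specifies, it will have a p-value for change and a trend in proportions. It will have no planned statement on whether the care delivered was acceptable.

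**Working it through.** The protocol gives no sample size, alpha, effect size or threshold for Aim 2, so there is no stated figure to reproduce. The check is a comparison of texts, followed by a numerical illustration.

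**1. Question against analysis**

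| Place in protocol | What it concerns |
|---|---|
| Study goals and objectives, Aim 2 | Level: is basic quality care offered |
| Executive Summary, use of checklists | Level: is care adequately provided |
| Executive Summary and Program Research Evaluation, scale-up condition | Level: is quality acceptable |
| MESH Mental Health Program, definition | Level: items successfully completed |
| Quality of care data, scores | Change from baseline, tested against zero |
| Quality of care data, hypothesis | Change growing with time |
| Quality of care data, binary items | Proportions increasing with time |

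The first four rows concern a level and the last three a change. No section plans an estimate of the attained level as the Aim 2 result, and none compares it with a standard.

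**2. Illustration**

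Assumptions, none of them protocol values for this analysis:
- The score is the percentage of items completed.
- There are n = 8 nurses. The Qualitative outcomes evaluation section gives about eight for the four selected centers; the number of mentees in the checklist analysis is not stated.
- The SD of within-nurse change is 10, 15 or 20 points.
- The test is a one-sample t-test of mean change against zero, two-sided 0.05.

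Power comes from the noncentral t distribution with n − 1 = 7 degrees of freedom and noncentrality δ = (mean change / SD) × √n, where √8 = 2.828.

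| Scenario | Change | SD 10 | SD 15 | SD 20 |
|---|---|---|---|---|
| 20% to 45% | +25 | δ = 7.07, power 1.00 | δ = 4.71, power 0.98 | δ = 3.54, power 0.86 |
| 90% to 90% | 0 | 0.05 | 0.05 | 0.05 |
| 90% to 92% | +2 | δ = 0.57, power 0.08 | δ = 0.38, power 0.06 | δ = 0.28, power 0.06 |

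In the first row, 100 − 45 = 55% of items are still missed at the end, yet a significant result is likely. In the second and third rows at least 90% are completed, yet a significant result is unlikely.

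The starting level appears nowhere in δ. A rise from 65% to 90% is also +25 points, so with the same SD it gives the same power as 20% to 45%. The test treats those two outcomes alike. As worded, it would also reject for a decline.

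**The case against.** **Levels will be visible anyway.** Analysing trends in binary items produces the proportions themselves, and intervals around them could be left to a statistical analysis plan that is not shown. This is partly right: the data will be there. But the protocol does not leave the matter open. It names the test and the hypothesis for this aim, and they address a different question.

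**A standard may exist elsewhere.** Aim 2 points to the program objectives, and the appendices are listed as attached but not reproduced. This stands. It cannot be said that the program has no adequacy standard, only that the analysis section does not use one.

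**The process evaluation is an adjunct.** The primary outcomes are mental health status and daily functioning, and the scale-up condition also covers uptake and patient outcomes. This stands and limits the importance of the point. Acceptable quality is still one of the things the protocol says must be documented.

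**Stronger readings that the text does not support.** A reader might infer any of these:
- *A significant rise counts as a pass and a null result as a failure.* The protocol states no success rule for Aim 2.
- *Monthly change implies a separate test each month and an inflated false positive rate.* The hypothesis concerns a time trend and repeated measures are adjusted for, so a single longitudinal model fits the wording at least as well.
- *Baseline is one noisy observation.* Baseline is not defined, and several checklists could be pooled.
- *Centers that joined in 2012 and 2013 are already near the ceiling.* No data are given, and the section counts time from implementation or enrollment.

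**Conclusion.** The mismatch holds. Aim 2 asks about attained level, and the stated analysis covers only change and trend, so following the plan as written does not answer the aim. Favourable-looking results are possible with poor care, and null-looking results with good care.

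The size cannot be taken from the protocol, which gives no inputs. Under the illustrative assumptions the chance of a significant result is 0.86 to 1.00 for care that ends with 55% of items missed, and 0.05 for stable care at 90%. The conclusion does not rest on those values, because a test of change ignores the level whatever the SD or number of nurses.

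The change should be made before the checklist data are analysed. It does not touch the primary outcomes or the Aim 3 sample size.

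**What to change.** In the data analysis paragraph for routine quality of care data:

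1. Make the main Aim 2 result the attained level of each listed indicator: the proportion for binary items, and the mean score or percent of maximum for the two summed scores.
2. Report it overall and for a late part of the year fixed beforehand, with 95% confidence intervals that account for repeated measures within nurse.
3. Interpret it against a standard that the program takes from its own MESH MH objectives and records before analysis. The sponsor must supply that standard.
4. Keep the within-nurse change and time-trend analyses as supporting results.

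A single composite of all items completed is not advised, because completion is not defined for the two summed scores.

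The cost is small: revised wording, some extra reporting and one program decision on the standard. No new data are needed.
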